For the adolescent cohort, assuming a baseline sustainable-product usage rate of 5% and a projected postintervention uptake of 20%, with 80% power and 5% significance, the minimum required sample size was calculated as 304 adolescent girls per site using a standard formula for comparing 2-proportions formula. To account for clustering by school and community catchment, a design effect of 1.5 (based on an assumed intracluster correlation coefficient of 0.02 and an average cluster size of 25 girls, consistent with design effects reported in comparable school-based menstrual health cluster studies) was applied, giving a minimum requirement of 456 adolescent girls per site (total N=912) for the phase 2 sensitization cohort. Of these, a subgroup of 416 girls (n=208 per site) will be enrolled in the phase 3 product-use follow-up; this subgroup size was determined pragmatically in line with recommendations for feasibility and pilot studies, which emphasize that a fully powered comparative sample is not required at this stage but that sample size should still be justified in relation to the primary feasibility objectives (recruitment, retention, and product continuation) rather than a hypothesis-testing end point [22,23]. A minimum of 30‐35 participants per arm per site is considered adequate to estimate continuation and acceptability proportions with reasonable precision (95% CI width ≤±16%) for feasibility purposes, and the planned 203 girls per site substantially exceeds this threshold, allowing additional precision for the secondary comparison between MC and MP users. Twenty community health and education workers per site will be enrolled (total n=40) for training and postintervention assessment; this number reflects the total eligible cadre of ASHAs, ANMs, AWWs, and grade 8‐12 female teachers attached to the selected clusters at each site, and was not derived from a formal power calculation, consistent with standard practice for facilitator and trainer cohorts in implementation feasibility studies.

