### Phase 3: Intervention and Follow-up

A total of 416 adolescent girls aged 13‐19 years, equally divided between the 2 study sites, who complete the phase 2 sensitization and provide consent or assent for product use, will be allocated to either of the following:

MC group: receives a size-appropriate medical-grade silicone MC with instructional manual.MP group: receives 3 reusable MPs with instructional pamphlets.

Allocation to the MC or MP group will be based on participant preference following a structured counselling session in which both products, their insertion or use requirements, and maintenance needs are explained; girls who express no strong preference will be allocated using a randomization sequence generated in blocks of 4, stratified by site, to achieve approximately equal group sizes. This preference-informed allocation approach was chosen, rather than full randomization, because acceptability and correct use of MCs in particular are strongly influenced by willingness to use an internally inserted product, and forcing product allocation against strong preference was judged likely to compromise both retention and the validity of acceptability outcomes in a feasibility study of this nature; this deviation from a purely randomized design, and its rationale, is reported here transparently as recommended for feasibility study reporting [20].

Participants will receive free products along with instructional materials and menstrual-tracking diaries that record menstruation dates, school attendance, side effects, and usage challenges. Monthly follow-ups will occur through home visits at 1, 2, 3, 6, 9, and 12 months, conducted by trained community health and education workers using a structured follow-up checklist.

A 12-month follow-up duration was chosen in line with prior longitudinal descriptive work showing that adaptability and correct use of MCs typically stabilize only after several menstrual cycles of sustained use and support [25].

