Primary outcomes are product usage, continuation (proportion still using the allocated product at 12 mo), comfort, and acceptability (assessed using a structured acceptability scale administered at 1, 3, 6, and 12 mo, capturing ease of insertion or removal, comfort during daily activities, leakage experience, and overall satisfaction). Secondary outcomes include school absenteeism during menstruation, menstruation-related health complaints, and likelihood of recommending the product to others. FGDs conducted at 6 and 12 months will further explore facilitators and barriers to continued use.

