### Data Analysis

Quantitative data will be analyzed using SPSS (v25). Descriptive statistics (frequencies, means, and SDs) will be used to summarize participant characteristics and uptake. Paired 2-tailed *t* tests and chi-square tests will evaluate pre- and postintervention differences in knowledge, attitude, and practice scores. Multivariate logistic regression will examine predictors of product adoption and continuation, including site, residence type (urban or rural), age, product type (MC vs MP), and baseline knowledge and attitude scores, with statistical significance set at *P*<.05. Qualitative data will be analyzed thematically using NVivo (v14), following the 6-phase reflexive thematic analysis approach described above.

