### Strengths and Limitations

To our knowledge, this is the first study in India to evaluate both MCs and MPs through a community-driven, adolescent-focused intervention. It adopts a robust mixed methods design that integrates facilitator involvement, an explicit behavior-change theoretical framework, and a cost-effectiveness evaluation, with a prespecified approach to qualitative rigor and mixed methods integration. The engagement of grassroots health workers and educators enhances the contextual relevance and community reach of the study, and the inclusion of both urban and rural or peri-urban catchments at each site strengthens generalizability relative to earlier single-context studies. However, potential limitations include cultural resistance to product use, the risk of participant attrition over the 12-month follow-up period, the use of preference-informed rather than fully randomized product allocation (which may introduce selection differences between MC and MP groups), and limited generalizability beyond the 2 geographic sites studied.

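### The MC-vs-MP coefficient for continuation pools chosen and randomised products because allocation route is not a listed covariate; for adoption, which is undefined, product type may not exist

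*Protocol article*

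**What the plan says.** The Data Analysis section names one multivariable logistic model specification for "predictors of product adoption and continuation, including site, residence type (urban or rural), age, product type (MC vs MP"), followed by baseline knowledge and attitude scores, "with statistical significance set at *P*<.05". How a girl came to her product is not on the list.

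The Phase 3 section describes two routes. The leading one is choice: "Allocation to the MC or MP group will be based on participant preference following a structured counselling session". The residual one is chance: "girls who express no strong preference will be allocated using a randomization sequence generated in blocks of 4, stratified by site". The stated reason for allowing choice is that "acceptability and correct use of MCs in particular are strongly influenced by willingness to use an internally inserted product".

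Among the primary outcomes is "continuation (proportion still using the allocated product at 12 mo"), so every allocated girl has a product type for that outcome. Adoption has no definition. The nearest usage is in the sample size section, where uptake is assumed to rise from 5% to 20% in the phase 2 cohort of 912. The same section calls MC versus MP a secondary comparison. Strengths and Limitations concedes that preference allocation is something "which may introduce selection differences between MC and MP groups".

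**The concern.** Two different comparisons sit behind one coefficient. Among randomised girls, MC and MP users differ only by chance at the start. Among girls who chose, they may also differ in willingness to use an inserted product, and the protocol itself treats that willingness as a strong influence on acceptability and correct use. If willingness also affects staying with the product for 12 months, it confounds product and continuation in the choosing group, and the pooled coefficient inherits part of that confounding. Attitude and knowledge scores are proxies and will not remove it fully.

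At stake is the reading of the MC-vs-MP result. A small P value could be reported as one product holding its users better, when it reflects who picked it. The design contains a randomised comparison that would avoid this, but no section of the protocol uses the distinction in the analysis.

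The adoption outcome has a separate difficulty. A predictor must exist for girls with and without the outcome, and product type exists only for girls who were allocated a product.

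**Working it through.** The protocol states no figure for the MC-vs-MP regression, so there is none to reproduce. The check has four steps.

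**1. Covariates against allocation.** Listed: site, residence type, age, product type, baseline knowledge, baseline attitude. The allocation rule also generates route (preference or randomised), which is not listed.

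**2. How large the bias could be.** The share who chose is not given, so it was varied from 10% to 90%. Assumptions of the simulation:
- 416 girls, no true product effect, 600 replicates per setting.
- Unmeasured willingness, standard normal. Among choosers, the log-odds of choosing MC rise by 1.0 per SD of willingness. Randomised girls have a 50% chance of MC.
- Log-odds of continuation = 0.5 + g × willingness, with g = 0.5 or 1.0.
- Baseline attitude correlates 0.5 with willingness and is in the model. Site, residence, age, knowledge and clustering were not simulated.

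| Share choosing | Apparent OR, route ignored (g = 0.5; 1.0) | False positives at P<.05 | OR in randomised girls, with route and interaction |
|---|---|---|---|
| 10% | 1.05; 1.07 | 5%; 5% | 1.01; 1.02 |
| 25% | 1.10; 1.14 | 7%; 10% | 1.02; 0.99 |
| 50% | 1.17; 1.32 | 13%; 27% | 1.01; 1.00 |
| 75% | 1.26; 1.52 | 20%; 53% | 1.00; 1.01 |
| 90% | 1.32; 1.68 | 26%; 68% | 1.01; 0.98 |

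With route and its interaction in the model, false positives for the randomised contrast lie between 3% and 6%. The direction (favouring MC) follows from the assumed selection; the protocol does not fix it. The interaction is needed because the confounding lies inside the choosing group. A main effect for route compares choosers with non-choosers and does not separate the two MC-vs-MP contrasts.

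**3. Whether unequal shares of choosers add to it.** To date 104 girls have MC and 106 have MP (Results). Taking the blocks of 4 as 1:1, the randomised counts differ by at most 2 per site, so 4 in all. With r randomised to MC and r′ to MP, the chooser shares differ by r′/106 − r/104. The extreme is r = 104, r′ = 100: 100/106 − 104/104 = −0.057, about 6 points. Even if choosers continued 20 points more often than randomised girls (assumed), the artefact would be 0.057 × 20 = 1.1 points. Selection on willingness in step 2 is therefore the mechanism that matters.

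**4. Precision of the randomised contrast.** 95% half-width = 1.96 × √(2 × 0.25 / n per arm), with n per arm = 416 × (1 − share choosing) / 2, at a proportion of 50%:
- 10% choose: n = 187, ±10 points
- 50%: n = 104, ±14 points
- 75%: n = 52, ±19 points
- 90%: n = 21, ±30 points

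Using the Abstract's 406 instead of 416 gives ±14 at 50% and ±31 at 90%.

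**Adoption.** If it means uptake among sensitised girls, 912 − 416 = 496 planned girls have no product type, and a complete-case fit would drop them. If it means use among allocated girls, product type is defined for all. The text does not say which. Mixed Methods Integration lists uptake and continuation as separate domains, which fits the first reading without settling it.

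**The case against.** The strongest defence is that the model seeks predictors, which is an associational aim; that phase 3 is sized for feasibility and not for a hypothesis test; that the selection problem is openly conceded; and that the covariate list is introduced as non-exhaustive in a condensed article, so a fuller analysis plan may add route. Much of this stands. The omission can only be put as route not being among the listed covariates, and the pooled coefficient keeps a meaning as an adjusted association. What does not stand is that the concession settles the matter, since it changes nothing in the analysis. The contrast is still tested at the 5% level, and the hypothesis-generating label under Representativeness and Subgroup Considerations covers residence and school type, not product.

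A reader might infer more than the protocol supports:
- That most girls chose. No share is given, and 104 versus 106 is compatible with many shares.
- That choosers persist more and are concentrated in one arm, producing a large artefact. Step 3 of the working rules this out on accrual to date. The protocol also says only that forcing a product against a strong preference could harm retention, not that choosers outlast indifferent girls.
- That the adoption model cannot be fitted. This holds on one of two readings.
- That the MC-vs-MP result has no interpretation. It lacks a causal one.

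**Conclusion.** The point holds in limited form. As listed, the continuation model gives one MC-vs-MP coefficient that combines a self-selected and a randomised contrast, and it should not be read as a product effect. With few choosers the distortion is negligible (odds ratio 1.05 to 1.07 at 10%). With many it is material (1.32 to 1.68 at 90%, with 26% to 68% false positives). These figures rest on the assumed strength of selection and on an unknown share of choosers; they show a range and do not estimate the bias in this study. Separately, adoption and its analysis population are undefined, and product type cannot serve as a predictor if that population includes girls without a product. Both matters can be settled before the analysis planned for the first quarter of 2027.

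**What to change.** - Retain allocation route (preference or randomised) for every phase 3 girl, including the 210 already allocated.
- In the continuation and acceptability models, include product, route and their interaction.
- Report MC versus MP among randomised girls as the unconfounded estimate, stating that it applies to girls without a strong preference. Report the preference girls separately as descriptive.
- Label any pooled MC-vs-MP contrast as associational.
- Define adoption and the girls in whom it is analysed, and remove product type from any adoption model that includes girls without a product.

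The cost is one variable that was necessarily known at allocation, plus wording. The drawback is the imprecision shown in step 4: if nearly all girls chose, the randomised estimate will say little, and the report should then give that interval and not fall back on the pooled coefficient as a product effect.

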### Phase 2: Adolescent Sensitization and Recruitment

The sensitization intervention will be conducted in small-group workshops (approximately 20‐25 girls per group) using materials developed and validated in phase 1, covering menstrual health, hygiene, and correct usage of MCs and MPs. Sessions will be led by previously trained community health and education workers (ASHA, ANM, AWW, and female teachers), ensuring cultural sensitivity and local relevance, and will run for approximately 90 minutes across 2 sessions per group. Adolescents will be recruited as per the inclusion criteria above through school registers (for school-going girls) and community health worker household lists (for out-of-school girls), with information sessions held for parents and guardians prior to enrollment. Preintervention and postintervention questionnaires (structured, self-administered, in the local language) will measure changes in knowledge, attitudes, and perceived readiness to adopt MC and MP, using the same core knowledge and attitude domains as the phase 1 instrument, adapted to the adolescent literacy level. Additionally, 2 focus group discussions (FGDs) will be held at each site—one with adolescent girls and one with their female guardians—to explore barriers and facilitators to product adoption, using a semistructured topic guide based on the COM-B framework (Multimedia Appendix 2). Quantitative data will be analyzed using SPSS (version 26; IBM Corp), and qualitative data will undergo thematic analysis to develop a comprehensive understanding of the social and behavioral influences on sustainable menstrual product adoption.

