### Representativeness and Subgroup Considerations

Given that grant-stage external review previously highlighted the importance of rural-urban variation, recruitment records will capture each participant’s residence type (urban, peri-urban, or rural, based on the Census of India classification) and school type (government, government-aided, or private, where applicable) at both sites. Sample composition by residence type and school type will be reported descriptively and used, where numbers permit, as covariates in the multivariate regression models described below, to allow exploration of whether uptake and continuation differ between urban and rural or peri-urban participants. Given the feasibility-study sample size, these subgroup analyses will be considered hypothesis-generating rather than confirmatory.

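### Perceived readiness to adopt is measured before product allocation but not named among the predictors of continuation, so the preference-based MC vs MP coefficient is open to confounding by a score already collected

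*Protocol article*

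**What the plan says.** All references are to the protocol article.

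- **Phase 2: Adolescent Sensitization and Recruitment.** The pre and post questionnaires "will measure changes in knowledge, attitudes, and perceived readiness to adopt MC and MP". Objective 2 also names readiness as something the campaigns should improve.
- **Phase 3: Intervention and Follow-up.** Product users are girls "who complete the phase 2 sensitization and provide consent or assent for product use". Both readiness scores are therefore planned to exist before a product is handed out. On allocation: "Allocation to the MC or MP group will be based on participant preference following a structured counselling session". Only girls without a strong preference are randomized, in blocks of 4 stratified by site.
- **Data Analysis.** "Multivariate logistic regression will examine predictors of product adoption and continuation", the predictors being introduced as "including site, residence type (urban or rural), age, product type (MC vs MP), and baseline knowledge and attitude scores", "with statistical significance set at *P*<.05". The pre-post tests are described for "differences in knowledge, attitude, and practice scores". Readiness appears in neither sentence.
- **Representativeness and Subgroup Considerations.** Residence type and school type are to serve, where numbers permit, "as covariates in the multivariate regression models described below". Subgroup analyses are called hypothesis-generating.

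**The concern.** The regression takes two of the three domains that the phase 2 questionnaire measures and does not name the third. No reason is given. The choice matters most for product type, because that predictor is largely self-selected.

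The protocol's own reason for not randomizing everyone is that acceptance and correct use of the cup depend heavily on a girl's willingness to use an internal product, and that allocation against a strong preference would harm retention. By that reasoning, willingness affects both which product a girl receives and how she fares on it, which is the structure of a confounder. Perceived readiness is a planned pre-allocation measure that bears on willingness.

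At stake is the reading of the MC vs MP coefficient. One product could seem to be continued better when the girls who chose it were simply more ready to start.

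**Working it through.** The plan states no figure on this point, so there is nothing to reproduce. The check compares the sections and then illustrates size and cost under stated assumptions.

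**1. Timing and list.** Readiness is recorded in phase 2, allocation follows in phase 3, and the Data Analysis list omits readiness while naming its two companion scores. The score is available and is not named.

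**2. Size of confounding (assumed effects).** A large-sample simulation used 200,000 records per setting.

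- Attitude and readiness are standard normal with correlation 0, 0.3, 0.5 or 0.7.
- Product choice: logit P(MC) = g × readiness, with g = 0 or 0.5 per SD.
- Continuation: logit P = 0.8 + 0.3 × attitude + b × readiness + 0 × MC, with b = 0.3 or 0.7. The true product OR is 1.0.

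| Readiness drives choice? | b | Product OR, readiness omitted | Product OR, readiness included |
|---|---|---|---|
| No (g = 0) | 0.3 or 0.7 | 0.99 to 1.01 | 0.99 to 1.02 |
| Yes (g = 0.5) | 0.3 | 1.09 to 1.15 | 1.00 to 1.02 |
| Yes (g = 0.5) | 0.7 | 1.19 to 1.35 | 0.99 to 1.01 |

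The range within a row comes from the attitude correlation. At correlation 0.7, attitude already absorbs part of the bias (1.09 and 1.19).

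**3. Against sampling error.** Take 416 girls in two groups of 208 and assume 70% continuation. Ignoring covariates, clustering and attrition, SE(log OR) = √[2 / (208 × 0.7 × 0.3)] = √(2 / 43.68) = 0.214. A shift to OR 1.09 is ln 1.09 / 0.214 = 0.086 / 0.214 = 0.4 SE. A shift to OR 1.35 is 0.300 / 0.214 = 1.4 SE.

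A separate finite-sample simulation (N = 416, 1,500 trials per setting) imposed a 0.3 SD readiness gap between two groups with no true effect. Without readiness, P<.05 occurred in 16.5% to 22.7% of trials when readiness had a latent correlation of 0.5 with continuation, and in 8.7% to 10.4% at 0.3. With readiness included, the rate was 4.5% to 5.5%. The gap was imposed and is not estimated from anything in the protocol.

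**4. The attitude coefficient.** Its conditional OR in step 2 is exp(0.3) = 1.35. At correlations 0.3 to 0.7 it reads 1.45 to 2.10 without readiness and 1.33 to 1.36 with it. Whether that drop removes bias or removes a pathway depends on whether readiness follows from attitude.

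**5. Cost in parameters.** Site 1, residence 2 (three categories), age 1, product 1, knowledge 1, attitude 1 and school type 2 make 9; readiness makes 10. Events = 416 × min(continued, discontinued).

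| Assumed continuation | Events | Per parameter, 9 terms | Per parameter, 10 terms |
|---|---|---|---|
| 70% | 124.8 | 13.9 | 12.5 |
| 80% | 83.2 | 9.2 | 8.3 |
| 90% | 41.6 | 4.6 | 4.2 |

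With the abstract's 406 girls, the 70% row becomes 13.5 and 12.2.

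**The case against.** **The list is open.** It begins with an inclusive word, and school type is promised elsewhere without being repeated there. A final covariate list may sit in an analysis plan that is not shown. This stands as far as it goes: readiness is not named, and no section excludes it. But a list that names both companion scores steers the analyst away from the third.

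**Attitude may already do the job.** The phase 1 instrument describes the attitude domain as attitude to adopting these products, and phase 2 reuses that domain. Table 1 lists knowledge and attitude scores but no readiness scale. A reader might infer that readiness is the closest baseline measure of continuation. The document does not show this. Readiness may also vary little among girls who have all agreed to use a product.

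**Post-sensitization readiness is not a clean baseline.** It is an outcome of the campaign under objective 2 and may lie on the path from site, residence, baseline knowledge or attitude to continuation. If girls at one site continue more because they became more ready, that is a site difference worth reporting. This objection stands and determines which score goes where in the fix.

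**Low stakes.** Phase 3 is sized on feasibility aims, and the limitations already concede that preference-based allocation may produce selection differences. This is correct. It limits the weight of the point, but a conceded selection difference is a reason to use a relevant score already in hand.

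**Conclusion.** The point holds in a limited form. Readiness is collected before allocation and is not named in the model, although the protocol's own argument about willingness makes the MC vs MP coefficient open to confounding by it.

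The size is unknown. Under the assumed effects the product OR moves from 1.0 to about 1.1 to 1.35, and only if readiness influences product choice as well as continuation.

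Three stronger readings are tempting and not supported:

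- That the model adjusts only for knowledge and attitude. It also lists site, residence type, age and product type, with school type added elsewhere.
- That site or residence effects become false predictors without readiness. Readiness may carry those effects.
- That a primary result is invalidated. The continuation proportions do not depend on this covariate, and the regression explores predictors.

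**What to change.** In Data Analysis:

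1. Add the baseline (pre-sensitization) readiness score beside baseline knowledge and attitude in the adoption and continuation models. All three scores then come from the same time point.
2. For the MC vs MP continuation coefficient, add a sensitivity analysis using the last readiness score before allocation (post-sensitization). This is closer to the moment of choice and may capture more of the selection. State that it may mediate the site, residence, knowledge and attitude associations, so those coefficients should not be read from this model.

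If readiness is only an item within the attitude score, or is left out on purpose, say so instead.

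The data are already being collected, and analysis is planned for the first quarter of 2027, so the change can still be prespecified. It costs one parameter, which is affordable at 70% continuation but adds to a thin model at 90%. The attitude coefficient becomes less precise where the two scores correlate. The model remains exploratory.
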